#### Secondary outcomes

Secondary outcomes include optimal health indicators such as (a) increased compliance to medication as reported by family members; (b) a reduction in the quantity of salt, oil, sugar, and meat bought in a month; (c) an increased number of healthy food items prepared in the household in a month; (d) sticking to the diet chart and health calendar; (e) a reduction in or abstinence from alcohol consumption; (f) engagement in at least one physical activity; (g) increased engagement with family, friends, and church groups; (h) getting back to professional or academic life and attending work or school regularly; and (i) attainment of appropriate BMI(< 25 kg/m^2^). In addition, the outcomes included attending at least one group meeting, increased linkage with the community, formal and informal interactions with the community, utilisation of nongovernmental organisation (NGO) services, regularity in hospital visits, and decreased depression and anxiety.

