Programme evaluation	Group evaluation	Usefulness of group sessions, Utilisation of NGO services	4 month	8 month	12 month
	Other evaluation	Usage of health calendar, diary, etc.	4 month	8 month	12 month

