### Intervention components

#### Usual care arm

The usual care arm will undergo the first- and second-level assessment. Patients with HTN and/or DM in the control arm will also be referred to PHCs or encouraged to access their preferred health care facility.

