### Intervention content

Brochure for health education with information regarding the importance of medication adherenceInstructions to families to monitor treatment adherence and medication complianceSteps on how families can support (physically and emotionally) through reminders, positive encouragement, etcCommon strategies for behavioural risk management, such as the provision of a diet chart, healthy recipe book, health calendar, which is to be mounted on the kitchen wall, and pamphlets for simple and effective cognitive strategies such as relaxation techniques. ASHA workers will be responsible for implementing general interventions. They will explain in detail the aforementioned four strategies before handing out the brochures and pamphlets. The research team and CHSWs will perform monitoring and coordination during the intervention. One-day training will also be provided to all ASHA workers prior to the implementation of interventions.

In addition to the general intervention, participants in the treatment arm will be administered risk-group specific interventions as follows.

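### Diet-chart and calendar adherence, and probably group-meeting attendance, depend on things the Methods give only to the intervention arm, so comparing the arms on them measures delivery rather than benefit

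*Protocol article*

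**What the plan says.** The Secondary outcomes section of the Protocol article includes, as item (d), "sticking to the diet chart and health calendar". It goes on to say that "the outcomes included attending at least one group meeting", and further on it adds "utilisation of nongovernmental organisation (NGO) services".

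The chart and calendar come from the trial. Intervention content describes the general module as including the "provision of a diet chart, healthy recipe book, health calendar, which is to be mounted on the kitchen wall", and Materials for intervention counts such items as a major part of the package. Treatment arm, and the section on implementing the general intervention, assign that module to everyone in the intervention arm. In Table 2, ASHA workers create beneficiary groups as part of the social-risk module.

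For controls, Study design and setting allows nothing beyond assessment. Usual care arm states: "The usual care arm will undergo the first- and second-level assessment", and adds only referral to a PHC or encouragement to use a preferred facility. The abstract differs, saying that controls receive the general intervention.

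Table 1 has separate Programme evaluation rows. One covers "Usefulness of group sessions, Utilisation of NGO services" and another covers use of the health calendar and diary. Both are scheduled at 4, 8 and 12 months. The Statistical analysis section compares change from baseline between the arms, with estimates at baseline, 6 and 12 months and adjusted odds ratios for dichotomous outcomes. It excludes no listed outcome.

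**The concern.** An outcome supports a randomised comparison of benefit only if both arms can attain it and it is measured in the same way in both. Under the Methods text, a usual-care participant has no trial diet chart or health calendar to follow. If the group meeting means the programme's own groups, that participant has no group to attend either. A difference between the arms would then show that materials were handed out and groups were formed. Because the items sit in a list introduced as indicators of good health, the trial report could present proof of delivery as an improvement in secondary outcomes.

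The article also gives these items two roles: outcomes in the Secondary outcomes section, and programme evaluation in Table 1. The Table 1 schedule does not match the analysis described.

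**Working it through.** The plan gives no figure for this point, so there is none to reproduce. The check sets the sections side by side and then adds one piece of arithmetic.

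**1. Can controls attain the item?**

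| Item | Source in the intervention arm | Open to controls under the Methods? | Open to controls if the abstract is right? |
|---|---|---|---|
| Diet chart and health calendar | General module | No | Yes |
| Group meeting | Probably the beneficiary groups of the social-risk module | Probably not | Probably not |
| NGO service use | Linkage promoted in the social-risk module | Yes, because the NGOs already operate locally | Yes |

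**2. Can the stated analysis be run on the Table 1 data?** Programme evaluation is scheduled at 4, 8 and 12 months. The analysis uses baseline, 6 and 12 months. Only month 12 is common to both, and with no baseline value a change from baseline cannot be formed. Table 1 names calendar use and the usefulness of group sessions. It does not name the diet chart or group attendance explicitly, so the match is close but not exact.

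**3. What would a comparison show if health did not change at all?** Randomisation is by ASHA ward, 10 wards with 5 per arm (Study design and setting), so I work at ward level.

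- Possible allocations: 10!/(5! × 5!) = 252.
- Suppose every intervention ward has some use and every control ward has none. Only the observed allocation and its mirror image give so large a difference in mean ward use. Two-sided p = 2/252 = 0.0079, or 0.008, which is the smallest value that 5 against 5 wards can give.
- One user in each intervention ward is enough: 5/726 = 0.7% of that arm.
- If only 4 of the 5 intervention wards have any use, the four must fall in the same arm with any one of the 6 wards without use. That gives 6 allocations and 6 mirror images, so p = 12/252 = 0.048.

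The permutation test is my illustration; the article does not specify it.

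**4. What happens to the planned odds ratio?** With *a* users among 726 in the intervention arm and 0 among 726 controls, the odds ratio is [a/(726 − a)] / [0/726]. The denominator is zero, so there is no finite estimate.

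**The case against.** The strongest case on the other side has five parts.

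- **NGO use.** A reader might infer that at least three secondary outcomes are closed to controls, counting NGO service use as the third. The documents do not support that. Treatment arm describes the NGOs as existing resources in the community, so controls can use them. Greater use of existing services is also an effect worth comparing. The intervention promotes NGO use but does not own it.
- **Group meeting is undefined.** The outcome list does not say which meetings count. Table 1 and Table 2 point to the programme's groups, but Table 2 also has ASHA workers speaking at community meetings and does not say who may attend. Exclusivity is therefore probable, not established.
- **The abstract.** If controls do receive the general intervention, item (d) is attainable in both arms and the clearest example falls away. The Methods sections agree with each other against the abstract, but the contradiction is in the document and has to be resolved.
- **Size.** A reader might also quote a vanishingly small p-value from a patient-level test on 726 per arm. That treats patients as independent, although only 10 wards are randomised, and it needs an uptake rate that the article does not give.
- **Analysis of each item.** Table 1 already handles these items partly as process measures, and an analysis plan not shown may settle how each is analysed. That softens the point but does not remove it: this article calls them secondary outcomes and states a between-arm analysis without exception.

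The first four limit the scope and size of the point. None of the five removes the problem with item (d) as the Methods now read.

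**Conclusion.** The point holds for one item and probably for a second. Under the Methods text, adherence to the diet chart and health calendar depends on materials supplied only to the intervention arm. Group-meeting attendance is in the same position if it refers to the programme's groups. For these items a between-arm difference is built in: use in all 5 intervention wards and none in the control wards gives a ward-level p of 0.008 with no health effect at all.

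This rests on three assumptions: that the Methods, not the abstract, describe what controls receive; that the chart and calendar in item (d) are the trial's own; and that the group meeting is a programme group.

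A reader might go further and conclude that the trial's effectiveness findings as a whole are tilted. The documents do not support that. The primary outcomes, and secondary outcomes such as BMI, alcohol consumption, physical activity, depression and anxiety, and regularity of hospital visits, can be attained in either arm. This is a reclassification of one or two secondary items and is worth making because it is cheap.

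**What to change.** 1. Take diet-chart and calendar adherence, and attendance at programme groups, out of the between-arm secondary outcomes. Report them descriptively in the intervention arm as process or fidelity measures, next to the Programme evaluation rows of Table 1, and name the diet chart and group attendance there.
2. Define the group meeting. If it means the social-risk module's groups, use as denominator the participants to whom a group was offered.
3. Keep NGO service use as a comparative outcome, with the same question asked at the same times in both arms.
4. Reconcile the abstract's description of the control arm with Study design and setting, Usual care arm, Treatment arm and the general-intervention section. If controls do receive the chart and calendar, item (d) can stay comparative, provided that it is measured identically in both arms.

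The reclassification is a rewording of the outcome list and Table 1 and needs no new data. Keeping NGO use comparative may mean asking that question of controls as well, if the Programme evaluation rows were meant for the intervention arm alone. The price is one or two fewer secondary outcomes on which the intervention can appear favourable.

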### Participant recruitment and study procedure

Participants for the trial will be recruited according to eligibility criteria. Eligible families will be those with at least one family member with a confirmed diagnosis of HTN and/or DM. The medical records of the patient will be used to confirm the diagnosis. Informed consent will be obtained from all adult family members. In addition, family members must be either first-degree blood relatives or spouses of the patient. Bedridden and terminally ill patients will be excluded from the study. Participation will be completely voluntary and can be withdrawn at any point if they intent to.

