### Study outcomes

Collection of data at baseline and follow-up at 6 months and 1 year will involve (a) the first-level assessment that includes a survey for collecting information regarding basic sociodemographic factors and verbal screening for examining chronic conditions in potential participants and (b) the second-level assessment that includes the use of standardised questionnaires to collect information on treatment adherence, medication compliance, behavioural risk factors (diet pattern, physical activity, tobacco, and alcohol consumption), social risk factors (perceived social support, neglect, and inclusion), and cognitive risk factors (depression, anxiety, stress), as well as a semi-structured interview schedule for identifying the motivating and protective factors of participants. In addition, trained staff will conduct BP, blood sugar level, and BMI measurements in all participants at three time points (baseline and 6 and 12 months after baseline). Anthropometric measurements will include height (in cm), weight (in kg), and waist circumference (in inches). BP and pulse rate will be measured using electronic BP monitors ([name] BP-02 Blood Pressure Monitor). Trained interviewers used a lancet for finger prick to obtain fresh capillary whole blood and a glucometer to measure the random glucose level. HTN will be measured twice in the sitting position at two time periods, and the average of the two readings will be used as the final value. Detailed survey measures are described in Table 1.

**Table 1 Tab1:** Measurement domains and data collection time points

**Variables**	**Components**	**Measurement Tools**	**Baseline**	**6 months**	**12 months**
Sociodemographic variables		Age, sex, marital status, education, occupation, and family income	✔		
Behavioural measures	Tobacco use, Alcohol consumption, Diet Physical activity	Behavioural and Lifestyle Questionnaire	✔		✔
Cognitive measures	Depression Anxiety Stress	DASS scale	✔		✔
Clinical measures	Anthropometry	Waist circumference (measuring tape) Height (measuring tape) Weight (weighing machine)	✔	✔	✔
	Blood pressure	[name] Pressure Calculator			
	Blood sugar	Glucometer (finger prick method)			
Social measures	Social networks	Wenger’s social network typologies	✔		✔
	Social cohesion	Social cohesion questionnaire			
Treatment adherence	Compliance to medications Adherence to Health check ups	Questionnaire on health service utilisation	✔	✔	✔

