### Statistical analysis

Data will be analysed on the basis of the intention to treat principle. Changes observed from the baseline and at follow-up will be compared between the intervention and usual care groups. All data will be de-identified using a unique ID to ensure the confidentiality of information. Upon implementation of the intervention, follow-up measurements will be taken at 6 and 12 months from the baseline. Data will be generated from standardised questionnaires and assessment procedures. Baseline characteristics will be described using means (with standard deviations) or frequencies based on the type of variable. The mean difference between the groups will be examined to understand the effects of the intervention. Mixed effect analysis of covariance will be employed to test for interactions between time (pre and post) and group (intervention or usual care), and partial eta squared (ηp^2^) will be reported as a measure of effect size. The comparisons of variables will be adjusted for potential confounders. The intention-to-treat analysis will be used to observe changes occurred throughout the year during follow-up in participants assigned to the Swāsthya intervention and usual care. The effect attributable to the intervention will be estimated by calculating mean differences between the groups at each of the follow-up points (at the baseline and at 6 and 12 months after the baseline; adjusted odds ratios for dichotomous outcome variables at 95% confidence intervals). Precautions will be taken to rule out the potential interaction effects between the Swāsthya and usual care groups. Software-assisted multiple imputation methods up to five times will be used to deal with missing values. All statistical analyses will be performed using STATA-14 and R software. The effectiveness of the intervention model will be ascertained 1 year after the completion of the study, and the model in itself will also be made public. Information on the study will be available on the website of the college as well as reported in scientific journals and at scientific conferences.

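### The secondary BMI outcome is a bare threshold (below 25) with no denominator, visit or lower limit, and is weaker than baseline-adjusted BMI from data already collected

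*Protocol article*

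**What the plan says.** Under Secondary outcomes, item (i) is "attainment of appropriate BMI(< 25 kg/m^2". The list attaches no visit to it, does not say which participants enter the denominator, and gives no lower limit.

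The entry rule under Participant recruitment and study procedure concerns diagnosis only: "Eligible families will be those with at least one family member with a confirmed diagnosis of HTN and/or DM". The clinical exclusion is "Bedridden and terminally ill patients will be excluded from the study". Neither refers to weight or BMI.

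Under Study outcomes, "trained staff will conduct BP, blood sugar level, and BMI measurements in all participants at three time points", namely baseline, 6 and 12 months. Table 1 likewise schedules anthropometry at all three.

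Statistical analysis gives general methods without assigning one to BMI. For binary outcomes it plans "adjusted odds ratios for dichotomous outcome variables at 95% confidence intervals". It also says "Mixed effect analysis of covariance will be employed to test for interactions between time (pre and post) and group (intervention or usual care", plans mean differences at each time point, and states that "Changes observed from the baseline and at follow-up will be compared between the intervention and usual care groups".

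**The concern.** The label is 'appropriate' BMI, but the criterion is one-sided. Read literally, three kinds of participant count the same: someone who moved from above 25 to below it, someone who was below 25 throughout, and someone whose BMI is very low. With no BMI entry criterion, the second kind may be a large share.

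A participant who loses weight but stays above 25 contributes nothing. Reaching the cut requires a weight loss of 1 − 25/28 = 10.7% from BMI 28 and 1 − 25/30 = 16.7% from BMI 30.

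At stake is whether this outcome can show a modest weight effect, and whether a reader can tell what a reported proportion means. A binary state is a weak use of a measurement taken in every participant at three visits.

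**Working it through.** **The plan's own figure.** The article states no power, effect size or expected rate for BMI, so there is nothing to reproduce. The only document figure used here is 726 per arm (Sample size).

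**Assumptions (none is in the article).** BMI is normal with the same SD at both visits: mean 24.5 or 26; SD 4 or 4.5; baseline to follow-up correlation r 0.80, 0.90 or 0.95. The true shift is 0.4 kg/m² downward in the intervention arm. Participants are treated as independent.

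**Step 1. Already below 25 at baseline:** Φ((25 − mean)/SD).
- Mean 24.5, SD 4: Φ(0.125) = 55.0%.
- Mean 26, SD 4.5: Φ(−0.222) = 41.2%.
- Over all combinations: 40% to 55%.

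By simulation, 73% to 88% of intervention-arm successes at follow-up were already below 25 at baseline.

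**Step 2. Very low BMI.** With an illustrative cut of 18.5 (not in the article), 9% to 18% of intervention-arm successes fall below it. This uses the lower tail of a normal curve. If BMI is right-skewed, the share would be smaller.

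**Step 3. Unadjusted proportion below 25:** z = (p1 − p0)/√(2p̄(1 − p̄)/726).
- SD 4, mean 26: p0 = 0.401, p1 = 0.440, z = 1.51.
- SD 4.5, mean 26: p0 = 0.412, p1 = 0.447, z = 1.34.

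**Step 4. Continuous BMI adjusted for baseline:** SE = SD × √(1 − r²) × √(2/726); z = 0.4/SE.
- SD 4, r 0.95: SE = 0.0656, z = 6.10.
- SD 4.5, r 0.90: SE = 0.1030, z = 3.89.
- SD 4.5, r 0.80: SE = 0.1417, z = 2.82.

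**Step 5. Logistic regression of BMI below 25 on arm and baseline BMI.** Simulated with 1,000,000 per arm, z multiplied by √(726/1,000,000).

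| SD | r | Unadjusted proportion | Baseline-adjusted logistic | Baseline-adjusted BMI |
|---|---|---|---|---|
| 4 | 0.80 | 1.5 | 2.0 | 3.2 |
| 4 | 0.90 | 1.5 | 2.4 | 4.4 |
| 4 | 0.95 | 1.5 | 2.8 | 6.1 |
| 4.5 | 0.80 | 1.3 | 1.8 | 2.8 |
| 4.5 | 0.90 | 1.3 | 2.1 | 3.9 |
| 4.5 | 0.95 | 1.3 | 2.5 | 5.4 |

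The two assumed means give nearly the same values. The fair comparison is between the last two columns, because both use baseline BMI. The squared ratio, for example (2.04/3.18)² = 0.41 and (2.81/6.10)² = 0.21, shows the adjusted binary analysis keeping about 21% to 42% of the information.

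**Step 6. The comparison without baseline adjustment.** For a normal variable cut at the point with share q below it, relative efficiency is φ(z_q)²/[q(1 − q)]. This is 64% at q = 0.5, 62% at 0.4 or 0.6, and 49% at 0.2.

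**Step 7. Restricting to baseline BMI of 25 or more.** From 726 × (1 − p0), about 327 to 435 per arm remain. Multiplying the Step 4 values by √(1 − p0) gives z of about 1.9 to 4.7.

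**Step 8. Clustering.** Ten wards give 1452/10 = 145.2 patients each. With an illustrative intracluster correlation of 0.01 applied to every analysis, the design effect is 1 + 144.2 × 0.01 = 2.44 and each z is divided by 1.56. The three ranges become about 0.9 to 1.0, 1.2 to 1.8 and 1.8 to 3.9. The ordering stays; the absolute values should not be read as the trial's power.

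**The case against.** The strongest reply is that this is one item in a long list of secondary indicators, and that the wording is ambiguous rather than wrong. 'Attainment' may mean crossing from 25 or above to below 25, in which case nobody already below 25 is counted. That reading is available. It still leaves the denominator unstated, the low end open and the cut-point in place.

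Second, Statistical analysis plans changes from baseline, mean differences, covariance analysis and adjusted odds ratios, so a continuous BMI analysis is not excluded and may be specified in a document not shown. This stands as far as it goes, but the outcome definition itself is binary, and the article does not assign BMI to the continuous methods.

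Three stronger readings are tempting and are not supported:
- **That the result would be biased.** Participants already below 25 occur in both arms and are balanced in expectation by randomisation, though only ten wards are randomised and chance imbalance is possible. The harm is dilution and unclear meaning.
- **That the outcome is almost blind to a weight effect, or that a real benefit would be reported as none.** With baseline adjustment, the binary analysis reaches z of 1.8 to 2.8 under the assumptions. Setting the unadjusted proportion against adjusted BMI overstates the cost of the cut-point, because much of that gap comes from baseline adjustment. Without adjustment on either side, the loss is about 36% to 51%, so usually not most of the information.
- **That only patients just above 25 can respond, or that the target is unattainable in obesity.** At SD 4.5 and r 0.90 the residual SD is 4.5 × √0.19 = 2.0 kg/m², so crossing is not confined to a narrow band. Attainability is a clinical judgement that the article does not settle.

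**Conclusion.** The point holds as a weakness in how a secondary outcome is defined. The definition lacks a denominator, a visit and a lower limit, and nothing in the eligibility criteria makes up for that. Baseline-adjusted continuous BMI uses data the trial already collects. Under the stated assumptions its z is about 1.6 to 2.2 times that of the best binary analysis (2.8 to 6.1 against 1.8 to 2.8).

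That ratio depends on the assumed BMI spread and correlation, and on clustering affecting both analyses alike. The textual part, an open-ended threshold with two possible denominators, needs no assumption. The trial's primary conclusions are not affected; the change is worth making but is not critical.

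**What to change.** Reword item (i) under Secondary outcomes. The main BMI analysis becomes the between-arm difference in continuous BMI at 12 months in all participants, adjusted for baseline BMI and accounting for ward clustering, with 6 months as support. Participants with baseline BMI of 25 or more form a supporting subgroup. They should not be the main population, because of the loss of precision in Step 7.

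Keep BMI below 25 only as a supporting summary among those at or above 25 at baseline, with its visit named. The investigators should state how low BMI is classified.

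No new data are needed; the change is to outcome and analysis wording. There are two downsides. A mean difference is harder to communicate than a proportion at target. Like the threshold, it also cannot separate intended weight loss from loss due to poor glycaemic control.
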